### Statistical analysis

The results of this trial for outcomes will be analyzed based on intention-to-treat (ITT), modified ITT (mITT), and per protocol (PP) approaches, with a primary consideration for mITT results. The ITT group will include all participants who are randomized after satisfying eligibility criteria. The mITT group will include participants who are randomized and who have received the study drugs at least once. The PP group will include participants in the mITT group who have completed the standard treatment for at least 20 of the 24 weeks for the control group or those who have completed the planned treatment for at least 10 of the 12 weeks for the investigational group. A safety analysis will be performed based on the safety group, which will include participants who have been administered with at least one dose of the investigational drugs.

For the primary outcome analysis, the frequency of occurrence of unfavorable outcomes in the control and investigational groups will be analyzed, and the incidence rate of unfavorable outcomes ($${\widehat{P}}_{T}, {\widehat{P}}_{C}$$) and the 95% confidence interval will be estimated. In this non-inferiority test, if the upper limit of the two-sided 95% confidence interval of the difference in incidence of unfavorable outcomes at 18 months between the investigational and control groups ($${\widehat{P}}_{T}-{\widehat{P}}_{C}$$) is less than 6%, it will be concluded that the investigational group is not inferior to the control group.

For the analysis of time to unfavorable outcome, time to culture conversion, and time to recurrence, the median time of each group will be estimated using the Kaplan–Meier method and will be compared with the log-rank test. Treatment success rate and recurrent rate at the end of treatment will be compared with the chi-square test or Fisher’s exact test between the two groups.

Safety will be assessed based on the occurrence of adverse events during the clinical trial period. The frequency and proportion of all adverse events, serious adverse events, and adverse events of grade 3 or higher will be summarized and compared using the chi-square test or Fisher’s exact test.

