### Control group

Participants randomized to the control group will receive standard treatment in accordance with the Korean guidelines for TB [17] and the World Health Organization guidelines [4]. Consequently, patients in the control group will be administered isoniazid, rifampicin, pyrazinamide, and ethambutol for 2 months, followed by isoniazid, rifampicin, (and ethambutol) for 4 months, comprising a total treatment period of 6 months (Table 1). Although temporary use of secondary anti-TB drugs is permitted in the case of adverse events such as liver toxicity, the total duration of use should be less than 4 weeks. If rifampicin is discontinued because of adverse events, the period of discontinuation must also be less than 4 weeks.

**Table 1 Tab1:** Dose and schedule of anti-tuberculous drugs for the control group

Drug name	Capacity			Administration method
	Per bodyweight	Recommended dose	Maximum dose	
Isoniazid	5 mg/kg	300 mg/day	300 mg/day	once a day before meal
Rifampicin	10 mg/kg	450 mg (< 50 kg) 600 mg (≥ 50 kg)	600 mg/day	once a day before meal
Pyrazinamide	20–30 mg/kg	1000 mg (< 50 kg) 1500 mg (50–70 kg) 2000 mg (> 70 kg)		once a day after meal
Ethambutol	15–20 mg/kg	800 mg (< 60 kg) 1200 mg (60–80 kg) 1600 mg (> 80 kg)		once a day after meal

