### Investigational group

Participants randomized to the investigational group will be treated with high-dose rifampicin (body weight, dose: < 44 kg, 1200 mg/day; 45–54 kg, 1500 mg/day; 55–64 kg, 1800 mg/day; 65–74 kg, 2100 mg/day; > 75 kg, 2400 mg/day), isoniazid (300 mg/day), and pyrazinamide (body weight, dose: < 50 kg, 1000 mg/day; 50–70 kg, 1500 mg/day; > 70 kg, 2000 mg/day) until culture conversion (liquid medium) is confirmed (Table 2). High-dose rifampicin and isoniazid will be administered until 12 weeks after the date of sputum culture negative conversion. The dosage of rifampicin will be maintained throughout the study duration. Ethambutol will not be included in the initial regimen to reduce the number of pills. However, in the instance that isoniazid or pyrazinamide is discontinued prior to the end of treatment, ethambutol may be added to the treatment regimen if the investigator decides that reinforcement of the drug is necessary. Although temporary use of secondary anti-TB drugs is permitted in the case of adverse events such as liver toxicity, the total duration of use should be less than 4 weeks. If rifampicin is discontinued because of adverse events, the period of discontinuation must also be less than 4 weeks. The study overview is provided in Fig. 1.

**Table 2 Tab2:** Dose and schedule of anti-tuberculous drugs for the investigational group

Drug name	Dose (body weight)	Administration method
Isoniazid	300 mg/day	once a day before meal
Rifampicin	1200 mg/day (< 44 kg) 1500 mg/day (45–54 kg) 1800 mg/day (55–64 kg) 2100 mg/day (65–74 kg) 2400 mg/day (> 75 kg)	once a day before meal
Pyrazinamide	1000 mg/day (< 50 kg) 1500 mg/day (50–70 kg) 2000 mg/day (> 70 kg)	once a day after meal

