^h^ The date of the end of treatment is determined according to the time of culture conversion to negative. A visit every 4 weeks until EOT and every 3 months after EOT. The test is not performed after EOT

^i^ If the 78-week visit (EOS) after randomization arrives earlier than the EOT + 12 M visit, the EOT + 12 M visit is omitted, and the EOS visit proceeds

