### Definitions

Culture of *M. tuberculosis* will be considered to be converted to negative when two or more consecutive cultures, taken at different visits, are found to be negative in liquid medium. When a participant cannot produce sputum after the first negative culture sputum, they will be considered as having achieved culture conversion. The submission date of the first confirmed negative sputum culture will be regarded as the date of culture conversion. If *M. tuberculosis* is found to be re-cultured two or more times following a negative culture conversion, this will be termed culture reversion [18]. Treatment success is defined as achieving negative culture conversion and maintaining negative cultures till the end of treatment.

The sum of treatment failure, recurrence, death during treatment (except for accidents and suicide), loss to follow-up, and withdrawal from the study will be designated as “unfavorable outcomes.” Treatment failure will be defined as participants who fail to achieve culture conversion during treatment period, or as participants using second-line anti-TB drugs for more than 4 weeks. Recurrence will be assigned to participants that indicate the presence of *M. tuberculosis* in sputum cultures for two or more times after the end of treatment.

Adverse events will be defined when undesirable medical events have occurred in participants, irrespective of a causal relationship with the treatment [19]. When adverse events result in death, life-threatening conditions, patient hospitalization or prolongation of existing hospitalization, persistent or significant disability or incapacity, or a congenital anomaly or birth defect, the events will be classified as serious adverse events. The severity of each adverse event will be assessed based on Common Terminology Criteria for Adverse Events (CTCAE) version 5.0 [20].

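### The per-protocol rule counts treatment on different clocks in the two arms; on its likeliest reading an investigational non-converter cannot qualify, while an adherent control non-converter can

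*Protocol article*

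**What the plan says.** The article's Statistical analysis section names three analysis sets (ITT, mITT, PP), "with a primary consideration for mITT results". PP is the mITT set restricted by a completion rule that differs by arm:

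- Control: the participant has "completed the standard treatment for at least 20 of the 24 weeks for the control group".
- Investigational: the participant has "completed the planned treatment for at least 10 of the 12 weeks for the investigational group".

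The courses behind these rules are built differently. Control treatment is of fixed length, "comprising a total treatment period of 6 months" (Control group). In the investigational arm three drugs are given until conversion is confirmed, and then: "High-dose rifampicin and isoniazid will be administered until 12 weeks after the date of sputum culture negative conversion" (Investigational group). Table 4, footnote h, confirms this: "The date of the end of treatment is determined according to the time of culture conversion to negative".

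Under Definitions, non-conversion is part of the primary endpoint: "Treatment failure will be defined as participants who fail to achieve culture conversion during treatment period", and treatment failure is one of the unfavorable outcomes. The same section narrows who counts as a non-converter: "When a participant cannot produce sputum after the first negative culture sputum, they will be considered as having achieved culture conversion".

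**The concern.** The two thresholds look matched because they are the same fraction, but they are fractions of different things. In control the denominator is the whole course. In the investigational arm a 12-week denominator fits no whole course, because the planned length is time to conversion plus 12 weeks. If the 12 weeks are the post-conversion phase, entry to PP requires conversion in one arm only, and conversion is an outcome that arises after randomization and feeds the primary endpoint.

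In a non-inferiority trial the PP analysis is there to show that the result was not produced by poor adherence. A set whose membership depends on an endpoint component in one arm, or that accepts very different amounts of treatment in the two arms, serves that purpose poorly.

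**Working it through.** **1. The plan's own figure.** Inputs from Sample size calculation: 10% unfavorable in both arms, margin 6 points, one-sided 2.5%, power 80%.

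n = (1.960 + 0.842)² × 2 × 0.10 × 0.90 / 0.06² = 392.4, hence 393 per arm. With 15% dropout, 393 / 0.85 = 462.4, hence 463 per arm and 926 in total. All three figures reproduce, and the PP rule does not affect them.

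**2. The fractions.** 20/24 = 10/12 = 83.3%. The percentages agree; what is counted does not.

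**3. Reading A: the 12 weeks are those after conversion.** This is the only 12-week period defined for the arm.

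- An investigational participant who never converts never starts the 12 weeks and cannot qualify.
- A control non-converter with 20 weeks of treatment qualifies and counts as unfavorable.
- Nothing is required before conversion, which is the only phase of the investigational regimen that contains pyrazinamide.

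**4. Reading B: any 10 weeks count.** With conversion at week 8 (an example), the course is 8 + 12 = 20 weeks and 10/20 = 50% qualifies, against 83% in control. Non-converters can then stay in, but so can participants who took half of the assigned course.

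**5. Size under Reading A, for PP only.** Let f be the fraction of the investigational arm that never converts. All of these are events and all are removed; control is left unchanged.

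- Investigational PP rate: q = (pT − f) / (1 − f), with PP size 393 × (1 − f).
- Chance of declaring non-inferiority: Φ((0.06 − (q − 0.10)) / SE − 1.96), with SE = √(0.10 × 0.90/393 + q(1 − q)/(393(1 − f))).

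f is an assumption, as is carrying the 10% control rate and 393 per arm over to the PP set.

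| f | PP difference when both true rates are 10% | PP difference when true rates are 16% vs 10% | Chance of declaring non-inferiority at 16% vs 10% |
|---|---|---|---|
| 0 | 0.00 points | 6.00 points | 2.5% |
| 0.5% | −0.45 points | 5.58 points | 3.7% |
| 1% | −0.91 points | 5.15 points | 5.5% |

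For f = 1% at 16% vs 10%: q = 0.15/0.99 = 0.1515, SE = 0.02365, (0.06 − 0.0515)/0.02365 − 1.96 = −1.60, and Φ(−1.60) ≈ 5.5%. The shift at equal rates is 0.91/6 = 15% of the margin, from about 4 of 393 participants.

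**6. The opposing effect under Reading A.** With uninterrupted treatment, the investigational threshold is reached at conversion + 10 weeks: week 14 for conversion at week 4, week 18 for conversion at week 8. The control threshold is week 20. A participant lost between those weeks stays in PP as unfavorable in the investigational arm and is removed in control. As an assumption, take the low end of the loss range in the article's Discussion (5.3%), spread evenly over 24 weeks in both arms: 5.3/24 = 0.22% per week. That is 2 × 0.22 = 0.4 points for conversion at week 8 and 6 × 0.22 = 1.3 points for conversion at week 4, against the investigational arm. The thresholds coincide for conversion at week 10, and the effect reverses after that.

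**The case against.** The strongest reply has four parts.

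- **PP does not carry the conclusion.** mITT is primary and keeps every treated participant, so non-converters count in both arms. This stands. A reader might infer that the trial's type I error is inflated; the documents do not support that, since the error figures above concern the PP analysis alone.
- **The asymmetry is narrow.** A reader might infer that all early deaths and losses leave the investigational PP set only. They do not: a control participant who dies or is lost before week 20 also fails the rule. The clearly one-sided group is adherent non-converters. This stands.
- **The direction is not established.** It is tempting to say that PP is biased toward non-inferiority. Step 6 shows an effect of similar size in the opposite direction, so the net sign is unknown. This stands too.
- **Non-converters are probably few.** At 2% or 3% non-conversion the same formula would give 11.0% or 20.2%, but the article offers no basis for such fractions. Its only related figure is that fewer than 1% of TB patients in South Korea are not cured (Discussion), and conversion by default after one negative culture reduces the number further. The 10% rate also includes losses and withdrawals, many of which PP would remove.

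It can also be said that the rule never mentions conversion, and that the full protocol may spell out the derivation. That makes Reading A an inference, though from the only 12-week period the article defines. It does not rescue the rule, because Reading B fails as well. Nor is this a detail merely left to a fuller document: the article states the rule, and the rule does not fit the arm that it governs.

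**Conclusion.** The point holds as a defect in a supporting analysis and should be fixed. The PP rule uses different clocks in the two arms. On the likelier reading it makes entry depend on a primary-endpoint component in the investigational arm only and ignores adherence before conversion. On the other reading it accepts about 50% of a 20-week course against 83% in control.

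Taken alone, the removal of non-converters is worth about 0.5–0.9 points of PP difference, and a PP one-sided error at the margin of about 3.7–5.5% instead of 2.5%. This assumes 0.5–1% non-converters, a 10% control rate and 393 per arm. An opposing effect of comparable size is plausible, so no net direction is claimed. The primary mITT analysis and the sample size are not affected.

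**What to change.** Reword the PP definition so that both arms use one clock: at least 83% of assigned treatment, counted from day 0 to the participant's own protocol-defined end of treatment. Keep in PP anyone who reaches treatment failure (including non-conversion) or death while adherent up to that event, and count them as unfavorable. The second sentence is needed because an investigational non-converter has no conversion date from which a planned end of treatment could be set.

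The cost is one reworded definition and a slightly more complex derivation. Drug-intake compliance is already scheduled at the treatment visits in Tables 3 and 4, so no new data are needed, and the sample size does not change.

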## Methods/design

### Study design

This investigator-initiated study is a prospective, multicenter, randomized, open-label, two-arm non-inferiority clinical trial. Participants with drug-sensitive pulmonary TB will be randomly assigned to one of two groups at a 1:1 ratio, and the study will be terminated 18 months after randomization.

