### Assignment of interventions: allocation

#### Sequence generation

The randomization table will be generated and will be reproducible via SAS 9.4 software, using the stratified block randomization method with a stratification factor of (1) acid-fast bacilli (AFB) smear positivity and (2) presence of diabetes. The Medical Research Collaborating Center (MRCC) of the Seoul National University Hospital will operate a web-based randomization system remotely.

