### Sample size calculation

The objective of this study is to determine whether the new regimen is non-inferior to the existing standard treatment. The primary outcome is an unfavorable treatment outcome at 18 months after randomization. Based on the existing study [21], a 10% unfavorable treatment outcome for the standard treatment (control group) and a 0% difference from the investigational group is assumed. To obtain a study with 80% power and a 2.5% one-sided significance level for the non-inferiority recognition limit of 6%, each group will contain 393 participants. Assuming a 15% dropout rate [22], the total number of study participants will be 926, resulting in 463 participants in each group. In the occurrence of participant withdrawal within 7 days of randomization, replacement participants may be recruited.

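### Randomization is stratified by smear status and diabetes, but the analysis as written has no stratum term: a small efficiency gain, available at no cost, is left unused

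*Protocol article*

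**What the plan says.** Under Sequence generation, the protocol article allocates by the "stratified block randomization method with a stratification factor of (1) acid-fast bacilli (AFB) smear positivity and (2) presence of diabetes". The Study design section fixes the ratio: participants are "randomly assigned to one of two groups at a 1:1 ratio".

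Under Statistical analysis, the primary decision rests on "the two-sided 95% confidence interval of the difference in incidence of unfavorable outcomes at 18 months between the investigational and control groups"; non-inferiority is concluded when its upper bound lies below 6%. The two rates are described as overall incidences per group, and the interval method is not named. For time to unfavorable outcome, time to culture conversion and time to recurrence, the median times "will be estimated using the Kaplan–Meier method and will be compared with the log-rank test". Treatment success, recurrence and adverse events are compared by chi-square or Fisher's exact test. Neither stratification factor is mentioned again.

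The Sample size calculation section states that "a 10% unfavorable treatment outcome for the standard treatment (control group) and a 0% difference from the investigational group is assumed", and that for "80% power and a 2.5% one-sided significance level for the non-inferiority recognition limit of 6%, each group will contain 393 participants". After a 15% dropout allowance, "the total number of study participants will be 926, resulting in 463 participants in each group".

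**The concern.** Stratified blocks keep the arms balanced on smear status and diabetes. If those factors predict the outcome, this balance removes the between-stratum part of the true variance of the difference. A standard error computed as if allocation were simple still contains that part, so the interval is somewhat too wide. Non-inferiority is judged on the upper limit, so a wider interval lowers the chance of success for the same data. An unstratified log-rank test also loses power when a strong prognostic factor is left out.

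What is at stake is efficiency and consistency between design and analysis. A false claim of non-inferiority does not become more likely.

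**Working it through.** **1. The plan's own figure.** Inputs from the Sample size calculation section: rate 0.10 in both groups, margin 0.06, one-sided 2.5%, power 80%. With the unstratified binomial variance,

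n = 2 × 0.10 × 0.90 × (1.960 + 0.842)² / 0.06² = 392.4, rounded up to 393 per group.

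Dropout: 393 / 0.85 = 462.4, rounded up to 463 per group, 926 in total. Both stated figures reproduce, and neither relies on stratification.

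**2. Crude precision at 393 per group.** Half-width = 1.96 × √(2 × 0.09 / 393) = 4.19 percentage points. Nominal power = 80.1%.

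**3. Stratified precision.** Replace 0.09 by v = Σ wₖpₖ(1 − pₖ) over the four smear-by-diabetes cells, holding the overall rate at 10%. The documents give no stratum prevalences or risks. The assumptions are 30–50% smear-positive, 20–30% diabetic, the two factors independent, and the same odds ratio (OR) for each.

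One case in full: 40% smear-positive, 25% diabetic, OR 2.
- Weights: 0.45 (neither), 0.30 (smear only), 0.15 (diabetes only), 0.10 (both).
- Risks: 6.1%, 11.5%, 11.5%, 20.7%.
- v / 0.09 = 0.9787, so v = 0.0881.
- Half-width = 1.96 × √(2 × 0.0881 / 393) = 4.15 points.
- Power, stratified = Φ(0.06 / √(2v/393) − 1.96) = 80.9%.
- Power, crude interval under balanced strata = Φ((0.06 − 0.0419) / √(2v/393)) = 80.3%.

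The fair comparison is between these last two lines, because balanced allocation already gives the crude estimate part of the benefit.

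Across the assumed prevalences:

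| OR per factor | Half-width, stratified (points) | Power, stratified | Power, crude with balanced strata | Net gain (points) |
|---|---|---|---|---|
| 1.5 | 4.18 | 80.3% | 80.1% | about 0.2 |
| 2 | 4.15 | 80.8–80.9% | 80.3% | about 0.5–0.6 |
| 3 | 4.07–4.09 | 82.1–82.3% | 80.7–80.8% | 1.4–1.6 |
| 4 | 4.00–4.02 | 83.3–83.7% | 81.1–81.2% | 2.2–2.5 |

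The largest narrowing is 4.19 − 4.00 = 0.19 points.

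**4. Simulation.** 40,000 trials per scenario, 393 per group, 40% smear-positive, 25% diabetic, stratified Wald interval. The type I error is one-sided, at a true difference of 6 points.

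| OR per factor | Power, crude | Power, stratified | Type I error, crude | Type I error, stratified |
|---|---|---|---|---|
| 1.5 | 80.4% | 80.8% | 2.5% | 2.6% |
| 2 | 80.5% | 81.3% | 2.5% | 2.7% |
| 3 | 80.9% | 82.7% | 2.3% | 2.7% |
| 4 | 81.3% | 84.1% | 1.9% | 2.5% |

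The gain is 0.4 to 2.8 points. The crude interval is valid and becomes mildly conservative as the factors become more prognostic. The simple stratified Wald interval runs slightly above 2.5% in places, which is a reason to name the interval method with care.

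**5. Time to culture conversion.** 3,000 simulated trials per scenario, with every input assumed: 393 per arm, exponential times, treatment hazard ratio 1.22, 50% smear-positive. With a smear-positive hazard ratio of 0.67, 0.5 and 0.4, power is 76%, 69% and 62% unstratified against 77%, 76% and 72% stratified. The gaps are 1, 7 and 10 points.

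**The case against.** The strongest reply is that this is silence in a condensed article. No interval method is named for the primary comparison, and a stratum-weighted interval is also a 95% interval for that difference. The full protocol or an analysis plan may already provide for it. This stands as a limit on the point: a reader might infer that the plan has decided to ignore the strata in the primary analysis, and the text does not say so. It has less force for the secondary tests. Log-rank, chi-square and Fisher are named procedures, and their stratified counterparts are different tests.

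The second reply is that the gain may be close to nil. Unfavorable outcomes include loss to follow-up and withdrawal. The Discussion section says that fewer than 1% of Korean TB patients could not be cured, while 5.3–25.2% were lost to follow-up. Nothing in the article shows that smear status or diabetes predicts such loss. This also stands, and it is why the lower rows of the primary-outcome table should not be treated as expected values.

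Three stronger readings are tempting and are not supported:
- *The sample size counted on the strata, so precision already paid for is being given away.* The 393 and 463 come exactly from the unstratified variance.
- *The crude analysis distorts the type I error in a harmful direction.* It stayed at 1.9–2.5%, on the safe side for a non-inferiority claim.
- *The gain is large.* A variance reduction of 13.8% can be obtained with 50% smear-positive, 25% diabetic, a risk ratio of 2.5 per factor and a 23.5% event rate (1 − 0.90 × 0.85, adding dropout to the 10%). That implies a baseline risk of 0.235 / (1.75 × 1.375) = 9.8% and a risk of 9.8% × 6.25 = 61% in smear-positive diabetics. The protocol plans on 10%, and nothing in it supports such a gradient.

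**Conclusion.** The point holds as a minor one. The design is stratified and the analysis as written carries no stratum term. The crude analysis is valid, and mildly conservative if the factors are prognostic. For the primary comparison, stratifying is worth about 0.2 to 0.6 power points by formula at an odds ratio of 1.5–2 (0.4 to 0.8 in simulation), and between 2 and 3 points at an odds ratio of 4. The half-width narrows by at most about 0.2 points.

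For time to culture conversion the gain may be larger, up to roughly 7–10 points if smear status strongly predicts conversion, but this is a secondary outcome and the inputs are illustrative.

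All the gains rest on assumed prevalences and effects. The direction does not depend on them as long as the factors are prognostic. This is neither an error in the sample size nor a threat to the primary conclusion.

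**What to change.** Before data are examined, state in the analysis plan:

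- **Primary:** a Mantel-Haenszel stratum-weighted risk difference over the four smear-by-diabetes cells, with a stratified 95% interval of a named type (Sato or Newcombe-type), its upper limit compared with 6%. With 1:1 allocation within strata, the Mantel-Haenszel weights are close to proportional to stratum size, so the quantity estimated is still essentially the overall difference.
- **Secondary:** stratified log-rank tests for the three time-to-event outcomes and Cochran-Mantel-Haenszel tests for the binary outcomes.
- **Sensitivity:** the crude risk difference with its unstratified interval.

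If the full protocol or analysis plan already specifies this, confirming it is enough. The cost is wording only: both factors must be recorded to randomize each participant, and the sample size does not change. Timing matters because the trial is open-label. If the upper limit falls near 6%, a choice between crude and stratified intervals made afterwards would be open to doubt.

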### Study outcomes

The primary outcome is the proportion of unfavorable outcomes at 18 months after randomization.

Secondary outcomes include time to unfavorable treatment outcomes, time to culture conversion on liquid medium, treatment success rate at the end of treatment, proportion of recurrence at 18 months after randomization, time to recurrence after treatment completion, and adverse events of grade 3 or higher during treatment.

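### Recurrence is to be compared at the end of treatment, where it is zero by definition, and Kaplan–Meier medians are planned for two endpoints too rare to reach them

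*Protocol article*

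**What the plan says.** All references are to the protocol article.

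- **Statistical analysis, time-to-event outcomes.** Three outcomes are handled by one sentence: time to unfavorable outcome, time to culture conversion and time to recurrence. For each, "the median time of each group will be estimated using the Kaplan–Meier method and will be compared with the log-rank test".
- **Statistical analysis, proportions.** "Treatment success rate and recurrent rate at the end of treatment will be compared" by chi-square or Fisher's exact test.
- **Study outcomes.** The recurrence outcomes are listed as "proportion of recurrence at 18 months after randomization, time to recurrence after treatment completion". The Abstract lists the same two.
- **Definitions.** Recurrence requires *M. tuberculosis* "in sputum cultures for two or more times after the end of treatment". It is one component of the composite unfavorable outcome, with treatment failure, death during treatment, loss to follow-up and withdrawal.
- **Sample size calculation.** At 18 months, "a 10% unfavorable treatment outcome for the standard treatment (control group) and a 0% difference from the investigational group is assumed".

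**The concern.** There are two separate faults in the same paragraph.

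The first is a contradiction about when recurrence is compared. The outcome list looks at 18 months after randomization. The analysis looks at the end of treatment, a moment before which the Definitions do not allow a recurrence to be counted. Taken literally, the analysis has no events in either arm, and the listed 18-month proportion has no matching comparison. Relapse after stopping is what a trial of shortened treatment most needs to show, so the time point should not be left to be settled after data from an open-label trial have accrued.

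The second is the choice of summary. A Kaplan–Meier median exists only if the estimated curve falls to 0.50. For two of the three time-to-event outcomes the plan's own event rate is far below that, so the one summary measure it names would be reported as not reached in both arms.

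**Working it through.** **1. The design figures reproduce.** Inputs from the Sample size calculation: 10% in both groups, and "80% power and a 2.5% one-sided significance level for the non-inferiority recognition limit of 6%, each group will contain 393 participants".

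n per group = (1.960 + 0.842)² × (0.10 × 0.90 + 0.10 × 0.90) / 0.06² = 7.849 × 0.18 / 0.0036 = 392.4, rounded up to 393. With 15% dropout, 393 / 0.85 = 462.4, rounded up to 463 per group and 926 in all. This matches the plan, so 10% is the rate the design rests on.

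**2. Median time to unfavorable outcome.**

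- Expected events per arm: 463 × 0.10 = 46.3 (393 × 0.10 = 39.3 on the pre-inflation number).
- Events needed for half an arm: 232 of 463 (197 of 393).
- End of curve: 1 − 0.10 = 0.90, against the 0.50 needed.

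Exact binomial probability that at least 232 of 463 participants have the event:

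| Event rate | Expected events | Probability |
|---|---|---|
| 10% (plan) | 46 | about 3 × 10⁻¹⁰⁵ |
| 25% (10% plus the 15% dropout, all counted as events) | 116 | about 4 × 10⁻³¹ |
| 40% (assumed) | 185 | about 7 × 10⁻⁶ |

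The 25% row is a deliberate overstatement, because loss to follow-up and withdrawal are already inside the composite.

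**3. Median time to recurrence.** The document gives no separate recurrence rate. Recurrence is a component of the composite, so under the plan's assumption it accounts for at most about 46 participants per arm. Even if all 46 were recurrences, ignoring censoring, half of those at risk would have recurred only if no more than 2 × 46 = 92 participants had finished treatment, which is 92 / 463 = 20% of the arm.

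**4. Check with censoring.** Kaplan–Meier curves were simulated for 1,000 arms per scenario, with an assumed 15% censored at random times. For unfavorable outcome, 463 per arm were used at event rates of 3%, 6%, 10% and 25%. For recurrence, an assumed 440 per arm were followed from treatment ends between 14 and 24 weeks, at assumed rates of 2%, 5% and 10%. No arm reached a median in any scenario.

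**5. Recurrence at the end of treatment.** No arithmetic is needed. The Definitions require positive cultures after the end of treatment, and Tables 3 and 4 place the first scheduled follow-up visit 13 weeks after it. At the end of treatment the count is 0 in both arms, and a chi-square or Fisher test has nothing to compare.

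**The case against.** **The time point may be loose wording.** Treatment success at the end of treatment is a listed outcome, and recurrence may simply have been joined to it in one sentence. That is plausible: the Abstract and Study outcomes both give 18 months, and nobody would knowingly test zero against zero. This limits the consequence but does not remove the contradiction, because as written the phrase governs both rates.

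**An unreached median is not a failed analysis.** A reader might infer that two secondary outcomes would yield no estimate. The document does not support that. It specifies the Kaplan–Meier method and a log-rank test; the curves give event-free proportions throughout follow-up, and the log-rank test compares whole curves without a median. For unfavorable outcome, the 18-month proportions and their difference with confidence intervals are already the primary analysis. What is lost is one descriptive summary.

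**Recurrence does not depend on the faulty phrase alone.** It also counts in the primary composite at 18 months and has its own log-rank comparison. It would be wrong to conclude that the trial fails to assess it.

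**The origin of time to recurrence.** A reader might add that counting from treatment completion compares subsets formed after randomization, and ask for a randomization origin with death as a competing event. But the outcome is openly defined from completion in the Abstract and Study outcomes. Changing it would redefine an outcome on a debatable preference, and the risk set and censoring rules commonly belong to documents not shown here.

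**Higher event rates.** One might add the national loss-to-follow-up range in the Discussion (5.3–25.2%) to the 10%. That double-counts, since losses are already in the composite, and the conclusion does not need it.

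**Conclusion.** The point holds in two parts, both confined to secondary analyses.

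The recurrence comparison at the end of treatment is empty by the protocol's own definition and contradicts its own outcome list. This part rests on the text alone and needs no numerical assumption.

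The Kaplan–Meier medians for time to unfavorable outcome and time to recurrence are expected not to be reached. This rests on the plan's 10% assumption and has a wide safety margin, since even a 40% event rate would almost never produce a median. The correct description is not reached under the design assumptions, rather than impossible to define. The median for time to culture conversion is not in question, because most participants are expected to convert.

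The primary endpoint, the 6% margin, the non-inferiority rule and the sample size are unchanged.

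**What to change.** In the Statistical analysis section, and in the analysis plan if it repeats the wording:

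1. Compare the proportion with recurrence at 18 months after randomization, as the Abstract and Study outcomes state, and keep the end of treatment as the time point for treatment success only.
2. Keep the Kaplan–Meier median for time to culture conversion.
3. For time to unfavorable outcome and time to recurrence, report Kaplan–Meier cumulative incidence per arm with 95% confidence intervals alongside the log-rank test. For recurrence, add the between-arm difference with its 95% confidence interval. For unfavorable outcome, the 18-month difference is already given by the primary analysis.

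The cost is a few lines of text. No outcome is redefined, and no data, visits or participants are added.
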